### Randomisation

An independent statistician prepared the randomisation lists. All clusters were randomised at the beginning of the trial using a blocked scheme to ensure similar numbers of clusters were assigned to each group. Randomisation was stratified by (1) location (BHDSS or FWHDSS) and (2) a binary variable of ‘high’ or ‘low’ cluster-level incidence of clinical pneumonia (which correlates with VT pneumococcal carriage prevalence). Randomisation was carried out using the above stratification until restricted selections were achieved in which Basse and Bansang towns were in either trial group (the only two hospitals in the trial area are in Basse and Bansang), there was a balance in terms of the presence of a health facility in allocated clusters (i.e. six in one group and five in the other group), and there was balance on total population size between the two groups (i.e. <10% difference in the two groups). Random allocation was performed and revealed in a public event in which one of 100 valid randomisation lists was randomly selected.

All resident infants are eligible for enrolment in the trial, according to the cluster allocation of their village of residence. Consent is sought for the enrolment of infants at EPI clinics to receive the interventions. Consent is also sought for the investigation of patients presenting to health facilities who are under surveillance for clinical endpoints, and also from pneumococcal carriage survey participants.

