#### Sample size calculation

Sample size calculations were based on the primary outcome of NP carriage of VT pneumococci in children aged 2–260 weeks with clinical pneumonia. Initial sample size calculations assumed an equal number of 60 participants measured for the primary endpoint in each cluster, that is, 2040 in each group and 4080 in total. Using Basse data from 2015, we assumed the prevalence of VT carriage to be 13% in both the standard and alternative schedule groups. The alternative schedule will be considered non-inferior if the upper limit of the two-sided 95% confidence interval for the prevalence ratio is ≤1.38 (0.18/0.13 = 1.38). Using Basse data, we estimated the intra-class correlation coefficient (ICC) to be 0.01–0.02. We calculated study power using the methods of Farrington et al. [15] and Donner et al. [16]. Using the more conservative value for ICC of 0.02, a minimum number measured for the primary endpoint per cluster of 60, with 34 clusters per arm (with design effect of 2.18) and *α*=0.05, a sample size of 2040 per arm will provide 93% power to test the non-inferiority of the alternative schedule.

To increase confidence in the study power, we simulated data using 2015 BHDSS data on cluster-wise VT carriage prevalence in children with pneumonia. The simulated data were designed to be similar to the villages included in this trial with respect to the mean carriage prevalence, as well as the variability in prevalence across clusters. Using 1000 simulated populations, each consisting of 68 clusters of 60 individuals, baseline prevalence of 10% and a largest acceptable increase of 4%, i.e. from 10% to 14% (i.e. non-inferiority prevalence ratio of 0.14/0.10=1.40), study power was ≥85% in most scenarios.

During the piloting of trial procedures, it became clear that the number of patients measured for the NP carriage endpoint would be quite variable among clusters with less than 60 patients in some clusters. Further simulations using local data on the variable numbers expected per cluster in 1 year (*N*=3948, median=33, range 7–506) and assuming VT prevalence of 16% in both groups demonstrated trial power of 90%. In order to maximise trial power, the primary outcome will be measured in all eligible patients in each of the 68 clusters with a total number ≥4080 included in the final year 4 analysis.

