### Timing of outcome assessments

#### Timing of primary endpoint assessment

The primary outcome of VT carriage in children with clinical pneumonia is measured continuously throughout the course of the trial among resident children presenting unwell to health facilities in the trial area. That is, the outcome is assessed whenever a resident child presents unwell to a health facility, at any age between 2 and 260 weeks. This outcome will be presented as prevalence at four time points measured using data collected during each of the 4 years of intervention. The primary endpoint will be analysed using data from year 4 of intervention, following the greatest observable accumulation of the effects of the two schedules. Based on the number of patients with clinical pneumonia enrolled after elapse of 11 months in year 4, the 12-month period may be extended by 1–2 months to achieve the required sample size. Table 2 shows the results of the relative impact of the alternative versus standard schedule on VT carriage prevalence in children with clinical pneumonia.

**Table 2 Tab2:** Results of vaccine schedule impact on the prevalence of vaccine-type pneumococcal carriage in children aged 2–260 weeks with clinical pneumonia

	Alternative schedule			Standard schedule			Adjusted prevalence ratio (95% CI)
	Number VT *Spn*	Number measured	Prevalence % (95% CI)	Number VT *Spn*	Number measured	Prevalence (95% CI)	
Year 1	n	N	n/N ()	n	N	n/N ()	x.y (95% CI)
Year 2	n	N	n/N ()	n	N	n/N ()	x.y (95% CI)
Year 3	n	N	n/N ()	n	N	n/N ()	x.y (95% CI)
Year 4	n	N	n/N ()	n	N	n/N()	x.y (95% CI)
^a^Age (weeks)							
2–12	n	N	n/N ()	n	N	n/N ()	x.y (95% CI)
13–40	n	N	n/N ()	n	N	n/N ()	x.y (95% CI)
41–104	n	N	n/N ()	n	N	n/N ()	x.y (95% CI)
105–260	n	N	n/N ()	n	N	n/N ()	x.y (95% CI)

^a^Age-stratified analyses in year 4

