### Analysis of populations and cohorts

#### Population-level analysis of populations and cohorts

##### Primary endpoint

Estimation of the impact of the schedules in the population incorporates both direct and indirect effects of the schedules in those aged <5 years in the geographic area. Measurement of the primary endpoint in year 4 of intervention allows time for the development of potentially differential impacts of the two schedules. The primary endpoint will be measured in all resident children aged 14–1826 days (2–260 weeks) presenting to health facilities in the study area with clinical pneumonia in year 4, assigning them to each group according to the group allocation of their village of residence, and regardless of whether the child was enrolled as an infant to receive the study intervention or number of PCV doses received (Table 1). Children eligible for selection for measurement of the primary endpoint will be (a) born in the HDSS, (b) resident in the HDSS in year 4, (c) aged 2–260 weeks on the day of presentation, and (d) present with clinical pneumonia at a health facility in the trial area. Neonates aged <14 days are excluded as pneumococcal carriage is low at this age and to avoid potential ascertainment bias due to clinical events in the early neonatal period that are unrelated to pneumococcal transmission. The primary endpoint is a measure of VT prevalence in children with clinical pneumonia and does not require follow-up. VT carriage prevalence in each trial group will be calculated with the denominator being number of children eligible for measurement.

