##### Other population-level endpoints

The population-level prevalence of VT pneumococcal carriage will be measured in years 3 and 4 using age-stratified random samples of all residents in the HDSS (Table 1). Age-stratified random samples of 60 participants will be selected in each cluster with a total sample size of 4080 in each year. Ten individuals in each randomly selected household will be randomly selected, 2:2:2:1:1:1:1 according to the age stratification (0–11 months, 12–23 months, 24–59 months, 5–9 years, 10–14 years, 15–44 years, and ≥45 years). The prevalence of VT carriage will be calculated for each cluster using the number of enrolled participants as the denominator.

The population-level prevalence of VT pneumococcal carriage in infants aged 6–12 weeks unimmunised with PCV will be measured in year 4 (Table 1). Eligible infants will be born to women resident in the HDSS, present to an EPI clinic, be 42–84 days of age, and not yet be immunised with a first dose of PCV. Sixty infants in each cluster will be randomly selected from eligible infants. The prevalence of VT carriage will be calculated for each cluster using the number of enrolled infants.

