#### Individual-level cohorts

Individual-level ITT and PP cohorts will only include children enrolled as infants at EPI clinics to receive the study intervention. The individual-level ITT cohort will be used to calculate the prevalence of VT pneumococcal carriage in resident study participants presenting with clinical pneumonia in year 4. The individual-level ITT cohort will include all resident participants enrolled to receive study interventions who present with clinical pneumonia, assigning them to the study groups according to the allocation of their village of residence at enrolment, regardless of age at enrolment, the schedule, or number of doses received. The denominator in prevalence calculations will be the number of eligible children with clinical pneumonia. Repeated events in one individual will be included with the related non-independence of events accounted for in the cluster-level effect included in the GEE model.

The individual-level PP cohort will be used to calculate the prevalence of VT pneumococcal carriage in study participants presenting with clinical pneumonia in year 4. The individual-level PP cohort will include fully vaccinated resident participants (see the ‘Definition and assessment of adherence to the intervention’ section), enrolled at ≤273 days of age who present with clinical pneumonia, assigning them to the study groups according to the village of residence at enrolment. The denominator in prevalence calculations will be the number of eligible children with clinical pneumonia in the individual-level PP cohort. Repeated events will be included.

Incidence endpoints will be analysed using the individual-level ITT cohort including all participants enrolled to receive the intervention, assigning them to the study groups according to the allocation of their village of residence at enrolment, regardless of age at enrolment, the schedule, or number of doses received. Event counting starts on the date of enrolment. Follow-up ends either at death, outmigration, or the end of the follow-up period, whichever is earlier.

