#### Population-level primary endpoint

The primary analysis will be assessment of the impact of the two schedules on VT carriage prevalence in resident children aged 2–260 weeks with clinical pneumonia. Interpretation will relate to whether the prevalence of VT carriage in a child who lives in a geographic area allocated to the alternative schedule is not greater than the non-inferiority threshold when compared to a child who lives in a geographic area allocated to the standard schedule.

The primary endpoint will be calculated as the proportion (prevalence) of children with clinical pneumonia who have NP carriage of VT pneumococci. The contrast between the two groups will be presented as a prevalence ratio, with ratios expressed as the prevalence in the alternative compared to standard schedule group. To account for cluster-level non-independence, the primary analysis will use generalised estimating equations (GEE) with a log link, binomial family, and exchangeable correlation structure. The primary analysis GEE model will include the stratifying covariates used in the randomisation of clusters: (i) cluster location in BHDSS or FWHDSS, (ii) cluster high or low baseline incidence of clinical pneumonia. Analysis will not include the other variables used to restrict the randomisation lists to ensure balance in the other baseline characteristics (see the ‘Randomisation’ section) [27]. Patients and clusters will be analysed according to their random allocation.

If the ratio of VT prevalence in the two groups is given by ρ = π_1_ : π_0_, where *ρ* is the true ratio between the prevalence in the alternative (π_1_) and standard (π_0_) schedule groups, the null hypothesis is H_0_ : *ρ* > 1.38, and the alternative hypothesis is H_1_ : *ρ* ≤ 1.38. The null hypothesis represents inferiority of the alternative schedule [13]. Non-inferiority will be established if the upper limit of the confidence interval around the prevalence ratio is ≤1.38.

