### Missing data

Missing data will be reported in tables and figures. Specific missing data will include NP pneumococcal carriage and serotype for resident children with clinical pneumonia, NP carriage in the community surveys, blood culture and chest X-ray results for hospitalised patients with suspected pneumonia, sepsis, or meningitis, and group allocation. We do not expect missingness for these variables to be greater than 2–3%. If the percentage of missing data is greater than 10% for any of the specified variables, we will consider methods to impute missing values and sensitivity analyses with imputed data.

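### The SAP gives two denominators for the primary VT prevalence, children eligible and children measured, and does not say which one governs

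*SAP article*

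**What the plan says.** Under Population-level analysis of populations and cohorts, Primary endpoint, the SAP lists four eligibility conditions: born in the HDSS, resident in year 4, aged 2–260 weeks, and presenting with clinical pneumonia at a trial-area facility. It then fixes the denominator: "VT carriage prevalence in each trial group will be calculated with the denominator being number of children eligible for measurement".

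Two other sections agree. Under Individual-level cohorts, for the ITT cohort: "The denominator in prevalence calculations will be the number of eligible children with clinical pneumonia" (the PP cohort has the same rule within its own members). Under Population-level primary endpoint: "The primary endpoint will be calculated as the proportion (prevalence) of children with clinical pneumonia who have NP carriage of VT pneumococci". Neither restricts the denominator to children with a swab result.

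Two other places point the other way. Table 2, under Timing of primary endpoint assessment, shows n/N by group and year, with N headed "Number measured". The Missing data section says: "Specific missing data will include NP pneumococcal carriage and serotype for resident children with clinical pneumonia". It expects no more than 2–3% missing and will consider imputation above 10%. It gives no rule for a child without a result below 10%.

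The Sample size calculation section intends that "the primary outcome will be measured in all eligible patients in each of the 68 clusters", which would make the two denominators equal. The Randomisation section, however, notes that "Consent is also sought for the investigation of patients presenting to health facilities who are under surveillance for clinical endpoints", so an eligible child can go unmeasured.

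**The concern.** A child with clinical pneumonia but no carriage result cannot enter the numerator. If that child stays in the denominator, the arithmetic is the same as recording no VT carriage. The reported prevalence is then the prevalence among measured children multiplied by the share measured.

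Equal coverage cancels in the ratio, although both prevalences are still too low. Unequal coverage does not cancel. The primary decision is a single threshold, an upper confidence limit of at most 1.38, and the trial is unmasked. The plan itself looks for differential ascertainment and access to care. Lower coverage in the alternative group would push the ratio towards non-inferiority, and lower coverage in the standard group would push it away. A plan written to settle choices before results are known should not leave two denominators open for its primary endpoint.

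**Working it through.** The plan states no figure for this effect, so there is none to reproduce. The check takes the eligible denominator literally and asks how far it would move the result.

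**Inputs from the SAP.** Margin 1.38; two-sided α of 0.05, so 2.5% in the deciding tail; standard-group prevalence 13%; 34 clusters per arm of 60, so n = 2040; ICC 0.02. The design effect reproduces: 1 + 59 × 0.02 = 2.18. Effective n = 2040 / 2.18 = 936 per arm.

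**Assumptions.** Swabbing is unrelated to carriage. The split of missing results between groups is not in the document, so a range is shown.

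**Step 1: group prevalence.** Reported prevalence = true prevalence × (1 − m), where m is the share unswabbed. At 13% and m = 3%, this is 0.13 × 0.97 = 12.61%.

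**Step 2: prevalence ratio.** Reported ratio = true ratio × f, with f = (1 − m_alt) / (1 − m_std).

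**Step 3: false non-inferiority rate at a true ratio of 1.38.** The alternative-group prevalence is 0.13 × 1.38 = 0.1794.

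SE(log ratio) = √[(0.87/0.13 + 0.8206/0.1794) / 936] = 0.110.

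Rate = Φ(−1.96 − ln f / 0.110).

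| Unswabbed, standard v alternative | f | 1.38 appears as | False non-inferiority rate |
|---|---|---|---|
| equal | 1.000 | 1.380 | 2.5% |
| 2% v 3% | 0.990 | 1.366 | 3.1% |
| 0% v 3% | 0.970 | 1.339 | 4.6% |
| 2% v 10% | 0.918 | 1.267 | 11.8% |
| 0% v 10% | 0.900 | 1.242 | 15.9% |

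In the opposite direction, 3% v 2% gives f = 1.010 (1.38 appears as 1.394) and 10% v 0% gives f = 1.111 (1.38 appears as 1.533). Both make non-inferiority harder to declare.

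**Step 4: after the repair.** With measured children as the denominator, f = 1 for any coverage under the same assumption, and the rate stays at 2.5%.

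**The case against.** The strongest reply is that the decision does not rest on the quotient in the Primary endpoint section. The ratio and its interval come from a GEE on individual-level data (Confidence intervals; Population-level primary endpoint), and such a model omits a child without an outcome unless someone enters a zero. The Missing data section lists these results as missing and contemplates imputing them, which makes no sense for values already coded negative. The plan also means to swab everyone eligible, so the two denominators should nearly coincide.

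Much of this stands. A reader might infer that the plan counts unswabbed children as non-carriers and so biases the primary ratio. The document does not support that: no section codes them negative, and the ratio moves only if the eligible denominator also governs the model dataset and coverage differs by group. A reader might also take the large error rates in the table as what to expect. They need about 10% unswabbed in one group, well above the 2–3% the plan anticipates.

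A third tempting step is to extend the point to the community survey, where prevalence is "calculated for each cluster using the number of enrolled participants as the denominator". In a carriage survey, enrolment may imply a swab, so that wording is not shown to be a fault.

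The reply does not reconcile the text. If the GEE drops unswabbed children, the group prevalences described in the Primary endpoint section and the modelled ratio rest on different children. The Supplementary figures on determination of the primary endpoint, not shown here, may give swabbing counts, but counts alone would not settle which denominator applies.

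**Conclusion.** The contradiction is real and concerns the primary endpoint: three sections define the denominator without requiring a result, while Table 2 and the Missing data section imply that a result is required. Followed literally, the eligible denominator understates prevalence in each group. Its effect on the ratio is conditional and, at the plan's expected missingness, small: about 1% at 2% v 3% unswabbed and about 3% at 0% v 3%, with false non-inferiority rates of about 3.1% and 4.6% against 2.5%. It becomes substantial only near the 10% trigger, and it can act in either direction.

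These figures assume that swabbing is unrelated to carriage, that the eligible denominator governs the model, and that the SAP's planning values for n, design effect and prevalence hold. The splits by group are assumed. The point deserves correction because it leaves a choice open on the primary analysis, not because a material bias has been shown.

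**What to change.** - In Primary endpoint, Individual-level cohorts (ITT and PP) and Population-level primary endpoint, set the denominator to children with a valid carriage result, as in Table 2.
- State that a child without a carriage or serotype result is missing in the GEE and is never coded negative.
- State how non-typeable isolates enter the numerator and denominator, identically in both groups and in line with the outcome definition, which says only that they are excluded.
- Report the numbers eligible and measured by group beside Table 2.

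The cost is a phrase in each of three sections, two clarifying sentences and two counts per group. No new data are needed.

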**Fig. 1 Fig1:**
[figure not shown]
Study timeline of percentage vaccination coverage over time among all resident children aged 0–260 weeks in the **A** standard 3+0 and **B** alternative 1+1 schedule groups

The primary endpoint will be analysed at the population-level including all resident children aged 2–260 weeks, born in the HDSS, who present with clinical pneumonia in year 4 assigning them to each group according to the group allocation of their village of residence regardless of whether the child was enrolled as an infant to receive the study intervention and regardless of PCV schedule or number of doses received (Table 1). Eligible children will be aged 14–1826 days on the day of presentation to the health facility during year 4. The first day of study intervention is defined as the day on which all eligible infants in the population had an opportunity to be enrolled. The first dose of study intervention was administered on 2 September 2019 and the first day on which all eligible infants in the population at the time had an opportunity to be enrolled was 7 October 2019. Thus, the first day of year 4 of intervention will be 7 October 2022. Year 4 surveillance will begin on 1 November 2022.

##### Other population-level endpoints

The population-level prevalence of VT pneumococcal carriage will be measured in years 3 and 4 using age-stratified random samples of all residents in the HDSS (Table 1). Age-stratified random samples of 60 participants will be selected in each cluster with a total sample size of 4080 in each year. Ten individuals in each randomly selected household will be randomly selected, 2:2:2:1:1:1:1 according to the age stratification (0–11 months, 12–23 months, 24–59 months, 5–9 years, 10–14 years, 15–44 years, and ≥45 years). The prevalence of VT carriage will be calculated for each cluster using the number of enrolled participants as the denominator.

The population-level prevalence of VT pneumococcal carriage in infants aged 6–12 weeks unimmunised with PCV will be measured in year 4 (Table 1). Eligible infants will be born to women resident in the HDSS, present to an EPI clinic, be 42–84 days of age, and not yet be immunised with a first dose of PCV. Sixty infants in each cluster will be randomly selected from eligible infants. The prevalence of VT carriage will be calculated for each cluster using the number of enrolled infants.

The incidence of radiological pneumonia will be calculated in each year of the study in population-level cohorts and over the 4-year period of intervention. Population-level cohorts will include all resident children 0–1826 days of age with follow-up starting on the day of birth or day of migration into the HDSS, or the follow-up start date, whichever is later. Follow-up ends at death, migration out of the HDSS, at 1826 days of age, or the end of the follow-up period, whichever is earlier. Follow-up observation time for children will be assigned according to the group allocation of their village of residence at the beginning of follow-up, regardless of later episodes of internal migration, whether the child was enrolled as an infant to receive the study intervention, and regardless of the PCV schedule or number of doses received. Repeated events in an individual will be included as the overdispersion parameter in the negative binomial model will account for the non-independence of these events. Follow-up observation time for children will be assigned according to the group allocation of their village of residence taking into account later episodes of internal migration, but regardless of whether the child was enrolled as an infant to receive the study intervention and regardless of the PCV schedule or number of doses received.

Analysis of VT IPD incidence will be calculated in each year of the study and over the 4-year period of intervention, at the population-level including resident children 0–1826 days of age with follow-up defined as for radiological pneumonia. Endpoints of all IPD and NVT IPD incidence (Table 1) will be analysed at the population-level using the same populations as defined for VT IPD incidence.

The clinical pneumonia incidence endpoint will include all resident children aged 0–1826 days. The incidence of clinical pneumonia will be calculated in each year and over the 4 years of intervention using the same populations as for radiological pneumonia.

Analysis of hypoxic pneumonia incidence will include all resident children aged 0–1826 days. The incidence of hypoxic pneumonia will be calculated in each year and the 4-year period of intervention using the same populations as for radiological pneumonia.

The analysis of incidence of clinical pneumonia associated with NP carriage of VT pneumococci will include resident children aged 14–1826 days. Incidence will be calculated in each year and over the 4 years of intervention using the same populations as for radiological pneumonia.

The incidence of hospitalisation will be calculated including all resident children 0–1826 days of age. Incidence will be calculated in each year and the 4 years of intervention using the same populations as defined for radiological pneumonia.

Analysis of mortality will include all resident children 0–1826 days of age. Incidence will be calculated in each year and over the 4 years of intervention using the same populations as defined for radiological pneumonia.

Analysis of the incidence of non-pneumococcal invasive bacterial disease and diarrhoea will include all resident children 0–1826 days of age. Incidence will be calculated in each year and over the 4-years of intervention in the same populations as defined for radiological pneumonia.

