In the community carriage surveys in years 3 and 4, we will sample 60 residents in each of the 68 clusters. The same assumptions and methods of power calculation as for the primary endpoint will apply. We assume ICC=0.02, 15% baseline VT carriage prevalence in both groups, and a ≤1.38 prevalence ratio derived from the non-inferiority margin of a ≤15% ‘loss of effect’ compared to the standard schedule. If the upper bound of the 95% confidence interval of our prevalence ratio comparing the alternative to the standard schedule clusters is ≤1.38, then the alternative schedule will be considered non-inferior. Following these assumptions, the community carriage surveys in years 3 and 4 will have power >94% if we collect 4080 samples evenly across 68 clusters (i.e. 60 per cluster).

Power for the tertiary endpoint of VT prevalence in PCV unimmunised infants aged 6–12 weeks (assume VT carriage prevalence of 10%) will be similar to that for the primary endpoint. The study is not powered to determine non-inferiority for other endpoints.

As opposed to the non-inferiority hypothesis that is specified for the primary endpoint in year 4, we will specify a superiority hypothesis for the analysis of year 2 data on VT prevalence in children with clinical pneumonia. Setting a 5% level of significance with a two-sided test, power of 80%, with ICC=0.02, and assuming prevalence of VT carriage in the control group is 22%, we wish to detect an absolute difference of ≥7%. That is, the smallest clinically significant difference that we wish to detect is equivalent to prevalence of 15% versus 22% in the two groups and a prevalence ratio of 15.0/22.0=0.68. Given these parameters, if we measure the endpoint in 25 individuals per cluster, we would need to include 29 clusters in each group, that is, a total of 58 clusters. We will measure the endpoint in all 68 clusters using all the available measurements of the endpoint in year 2.

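### The community survey samples ten people per household, but its stated power of over 94% has no household term; the size of the loss depends on a correlation the SAP does not give

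*SAP article*

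**What the plan says.** The sampling is described in the SAP article under Other population-level endpoints: "Age-stratified random samples of 60 participants will be selected in each cluster with a total sample size of 4080 in each year". Within a cluster, "Ten individuals in each randomly selected household will be randomly selected", across seven age bands in the ratio 2:2:2:1:1:1:1, which sums to ten.

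The power is given under Sample size calculation. For the surveys, "The same assumptions and methods of power calculation as for the primary endpoint will apply". The inputs are: "We assume ICC=0.02, 15% baseline VT carriage prevalence in both groups, and a ≤1.38 prevalence ratio". The result is that the year 3 and year 4 surveys "will have power >94% if we collect 4080 samples evenly across 68 clusters".

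The carried-over assumptions come from the same section: "Sample size calculations were based on the primary outcome of NP carriage of VT pneumococci in children aged 2–260 weeks with clinical pneumonia". On the correlation it says: "Using Basse data, we estimated the intra-class correlation coefficient (ICC) to be 0.01–0.02". It takes 0.02 as the conservative end and gives a design effect of 2.18 for 60 per cluster.

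Under Population-level VT prevalence in the community, the survey is analysed by GEE with an exchangeable structure at trial-cluster level, adjusted for age stratum and the randomisation strata, and tested against 1.38. The Confidence intervals section specifies robust standard errors. No household correlation appears anywhere in the article.

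**The concern.** A design effect of 2.18 equals 1 + 59 × 0.02. It treats two members of one household as no more alike in carriage than any two people in a cluster averaging 4000 residents. The SAP's own text makes a higher household correlation plausible. The section on the non-inferiority margin ties carriage prevalence to transmission. The survey baseline table records respiratory symptoms in household members, bed sharing and the number of under-fives in the household.

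The year 4 survey is a secondary endpoint with a formal non-inferiority test. The stated power also matters for reporting, because Presentation of results limits the non-inferiority figure to endpoints with enough power. If the power is overstated, a failure to show non-inferiority could be read as evidence against the alternative schedule when it reflects limited precision.

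**Working it through.** **Inputs from the SAP.** 2040 people per arm (34 clusters × 60), prevalence 15% in both arms, margin 1.38, cluster ICC 0.02 (range 0.01–0.02), and a two-sided 95% CI, which is one-sided 0.025 for the non-inferiority test. Ten people per household gives 60/10 = 6 households per cluster; this is derived, not stated.

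**Step 1: the plan's own figure.** With design effect DE = 1 + 59 × 0.02 = 2.18, on the difference scale:

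- margin = 0.38 × 0.15 = 0.057
- SE = √(2 × 0.15 × 0.85 × 2.18 / 2040) = 0.01651
- one-sided 0.025: Φ(0.057/0.01651 − 1.96) = 93.2%
- one-sided 0.05: Φ(0.057/0.01651 − 1.645) = 96.5%

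The stated figure is therefore approached, or met at one-sided 0.05, on the difference scale with one level of clustering.

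**Step 2: the planned decision rule, before any household effect.** On the prevalence-ratio scale:

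- SE(log PR) = √(2 × 0.85 / (0.15 × 2040) × DE)
- power = Φ(ln 1.38 / SE − 1.96), with ln 1.38 = 0.322
- ICC 0.02, DE 2.18: SE = 0.1100, power 83%
- ICC 0.01, DE 1 + 59 × 0.01 = 1.59: SE = 0.0940, power 93%

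**Step 3: add the household level.** Each sampled person shares a household with 9 others in the sample and a cluster, but not a household, with 50 others. Hence DE = 1 + 9ρh + 50ρc, where ρh is the correlation within a household and ρc the correlation between households of one cluster. Setting ρh = ρc = 0.02 returns 2.18. The SAP gives no ρh, so the values below are assumptions.

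| ρh (assumed) | DE, ρc 0.02 | Ratio-scale power | DE, ρc 0.01 | Ratio-scale power | Difference-scale power, ρc 0.02, one-sided 0.025 |
|---|---|---|---|---|---|
| 0.05 | 2.45 | 79% | 1.95 | 87% | 90% |
| 0.10 | 2.90 | 72% | 2.40 | 80% | 85% |
| 0.20 | 3.80 | 60% | 3.30 | 66% | 74% |

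On the variant kindest to the plan (difference scale, one-sided 0.05, ρc 0.02), power falls below 94% once ρh exceeds about 0.06.

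**The case against.** The strongest reply is that the planned ICC may have room for a household effect. The SAP calls 0.02 the conservative end of 0.01–0.02. With ρc = 0.01 the two-level design effect reaches 2.18 only when 9ρh = 0.68, that is ρh of about 0.076. At ρh = 0.05 it is 1.95 and ratio-scale power is 87%, above the 83% found at ICC 0.02 with no household term. This stands. A reader might infer that true power must lie below a figure restated at ICC 0.02 alone, and the document does not support that.

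A reader might also attribute the whole fall from over 94% to 60–79% to households. The step to 83% is a matter of scale; the household effect is only what follows it.

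Three further limits hold:

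- That the ICC came from pneumonia patients is inferred from where it appears; the text says only that Basse data were used. Had it come from a sample with the same household structure it would already contain this effect, but nothing says so.
- Six households per cluster assumes each can supply the full age quota, including two infants and two one-year-olds. If households fall short and more are visited, the household term shrinks. At five per household, DE = 1 + 4ρh + 55ρc; with ρh 0.10 and ρc 0.02 this is 2.50, giving 78% instead of 72%.
- Holding the age mix equal across households and modelling age may remove some of the between-household variation.

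Finally, Additional analyses already plans group-wise ICCs for the year 4 survey. These are at cluster level and will show the clustering that occurred, but they leave the stated power as it is.

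**Conclusion.** The point holds as a mismatch between the survey's sampling design and its stated power. The figure of over 94% describes a one-level sample, while the plan draws a two-level one. The omission is certain; its size is not, because it rests on an assumed household correlation.

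With ρh between 0.05 and 0.20 and ρc between 0.01 and 0.02, power under the planned rule runs from 87% down to 60%, taking ten people per household. The scale issue alone puts it at 83% at the ICC the SAP chose for the survey.

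The analysis is not in question. A reader might infer that the confidence interval is too narrow because the model has no household term. Provided households are nested within trial clusters, robust standard errors at cluster level also cover correlation within households. What needs correcting is a planning statement for a secondary non-inferiority test.

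**What to change.** Under Sample size calculation, replace the survey power of over 94% with power computed on the prevalence-ratio scale for the two-sided 95% CI, using DE = 1 + 9 × household correlation + 50 × cluster ICC. Either show it over cluster ICC 0.01–0.02 and a stated range of household correlations, or estimate both components from the year 3 survey without reference to arm. If households often supply fewer than ten people, use the achieved number per household in the formula.

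Keep the sample size, the fieldwork and the cluster-robust GEE. The only cost is a less favourable stated power.
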